
#### Subgroup analyses

We plan to examine potential moderators of intervention effectiveness, including community/study site, ethnicity, education level, health insurance status, and acculturation. The interactions between these variables and study group assignment will be modeled and significant interactions will be decomposed and graphed.

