### Aims and objectives

Our specific aim is to determine if a strategy in which CHWs deliver multimodality, home-based screenings results in an increase in the proportion of participants screened for all four conditions (HIV, HCV, CRC, and cervical cancer) as compared to a strategy in which patients are navigated to primary care by a CHW at one of our participating health centers. Our study will have over 95% power to examine our primary hypothesis that the CHW led multimodality screening strategy will result in a 15 percentage point increase in participants who are up to date in screening for these four conditions (three for men) as compared to a strategy of linkage to primary care. Secondary analysis will examine increases in screening for each of the four conditions individually. Subgroup analysis will include examining outcomes by race/ethnicity and by gender.

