### Sample size calculation

The baseline screening rates in our sample size calculation rates are obtained from our feasibility studies and local data. The overall sample size was chosen to ensure sufficient power to detect clinically meaningful effects associated with a 15% point increase in proportion of additional screening done in the home-based arm versus primary care arm using two-sided test for differences in proportion. Although we plan to conduct intention-to-treat analyses, in which all women lost to follow-up will be considered “unscreened,” we will also conduct analyses with lost to follow-up participants excluded. For these analyses, we need to account for attrition (21% in our previous study). In addition, in our subgroup analysis where we look at each individual test, we set alpha at 1.25% instead of 5% to account for multiple testing. Even with a 25% attrition rate, a proposed total sample size of 900 participants (450 per arm and 150 per site) will give us over 95% power for our primary outcome and 90% power for the subgroup analysis.

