### Statistical analysis

Prior to any analysis, data screening for accuracy will be conducted and will focus on several aspects. We will determine the amount, pattern, and randomness of missing data. Outliers will be identified observations that appear to be very high or very low, and decide how to proceed based on the presumed cause. We will also identify inconsistencies within a single variable and between variables. As there are various types of measurements, we will use various descriptive statistics to visualize the study data with the appropriate graphical displays. Initially, we will perform an explanatory data analysis; visually via graphics/plots such as scatter and box-whisker plots and numerically by descriptive statistics such as range, median, means, standard deviations for measurements taken on a continuous scale, and percentages, various types of cross-tabulations for measurements taken on a categorical scale. Corresponding confidence intervals for means and proportions will also be calculated. To have a better understanding of the relationships among different study measurements, parametric or non-parametric correlation coefficients, bivariate, and multidimensional cross-tabulations, scatter and box-whisker plots will be constructed. Prior to analyses, baseline differences of key covariates from the PC and HBT arm will be examined with respect to our primary and secondary outcomes, particularly those related to race, ethnicity, SES and education. We will also examine differences on key variables between subjects who completed the study and those lost to follow-up. Our primary analysis will consist of chi-squared testing for the differences in proportions among the PC versus HBT study arms. Several univariate and multivariate logistic regression models will be used to calculate odds ratios and corresponding 95% confidence intervals for exploring the result of the screening and the relation to various types of key study variables in addition to study arms. Two-way interaction terms between for various study variables and the study arms may need to be included in the models. Transformations of the continuous data in order to meet statistical assumptions may be undertaken if indicated. Type-1 error will be set to 5% (α = 0.05) for calculating confidence intervals and testing various hypotheses for the primary outcome. Adjustment of type-I error for multiple comparisons will be performed by controlling the family-wise type-I error rate at the 0.05 level. Standard diagnostic tools will be used to assess any model fit. All statistical analyses will be carried out using SAS® v9.4 for Windows (SAS Institute, Cary, NC, USA) and/or R-project for Windows.

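### Moderator interactions are followed up and graphed only if significant, from an open list that does not name gender; effects with intervals should be shown for every level of a fixed list

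*Protocol article*

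**What the plan says.** All references are to the protocol article.

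- **Subgroup analyses** gives the list: "We plan to examine potential moderators of intervention effectiveness, including community/study site, ethnicity, education level, health insurance status, and acculturation". The word introducing it leaves the list open, and gender is not on it. The follow-up rule is "The interactions between these variables and study group assignment will be modeled and significant interactions will be decomposed and graphed".
- **Aims and objectives** makes a commitment that does not depend on significance: "Subgroup analysis will include examining outcomes by race/ethnicity and by gender".
- **Statistical analysis**, the parent section, says of interactions: "Two-way interaction terms between for various study variables and the study arms may need to be included in the models". On error rates it says "Type-1 error will be set to 5% (α = 0.05) for calculating confidence intervals and testing various hypotheses for the primary outcome" and "Adjustment of type-I error for multiple comparisons will be performed by controlling the family-wise type-I error rate at the 0.05 level". It names neither the family nor the method. It describes the logistic models as meant for "exploring the result of the screening and the relation to various types of key study variables in addition to study arms".
- **Sample size calculation** uses the term subgroup analysis for the four single-test comparisons, sets 1.25% for them, and states that the sample "will give us over 95% power for our primary outcome and 90% power for the subgroup analysis".
- **Primary outcome** is being up to date on all needed tests: four conditions for women, three for men.

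**The concern.** Showing subgroup results only when the interaction is significant is a selective rule. Interactions shown because they passed a threshold tend to have exaggerated estimates. Those that miss it may be imprecise rather than absent, and a reader without the intervals cannot tell which. The open list adds a practical difficulty: a family-wise correction needs a known number of tests.

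Gender is the most natural moderator here, because the composite is built differently for women and men. It is promised in one section and not named in the section that sets out the analysis.

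At stake is what the trial can say about which communities or groups gain more or less from home testing. The main comparison is not affected.

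**Working it through.** **1. The plan's own power figure.** Inputs from Sample size calculation: 450 per arm, 25% attrition, a 15-point difference, two-sided alpha 5% (primary) and 1.25% (single tests). This gives 450 × 0.75 = 337.5 per arm, and 0.05/4 = 0.0125. No control rate is stated, so it was scanned from 0.1% to 84.9% with the pooled normal approximation. The lowest power is 97.5% at 5% and about 92% at 1.25%. Both stated figures hold for the analyses they belong to. No figure is stated for moderator interactions.

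**2. Number of tests.** Five named moderators; six with gender.

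**3. False moderators if the family-wise rule does not apply** (one outcome, each test at 5%, no true moderation).
- Independent tests: 1 − 0.95^5 = 22.6%; 1 − 0.95^6 = 26.5%.
- A simulation of 3,000 trials of 900 (35% v 50%, 300 per site, ethnicity mostly determined by site, other moderator distributions assumed): 22.1% and 26.2%.
- Correlation of 0.5 between the test statistics (assumed): 18% and 21%.

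The range is therefore about 18% to 26%. Some correlation is plausible, since Trial design/setting describes two of the three communities as predominantly of one ethnic group.

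**4. False moderators if the rule does apply** (Bonferroni as an example). The per-test level is 0.05/6 = 0.0083, and 1 − (1 − 0.05/6)^6 = 4.9%. The simulation gave 5.1%.

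**5. Chance that a large real interaction is displayed.** Assumptions: a moderator splitting the sample in half (225 per arm per half), control rate 35% in both halves, and effects of 7.5 and 22.5 points. The average effect is the planned 15 points.
- Home-testing rates are 42.5% and 57.5%.
- SE = √[(2 × 0.35 × 0.65 + 0.425 × 0.575 + 0.575 × 0.425)/225] = √(0.94375/225) = 0.0648.
- z = 0.15/0.0648 = 2.316.
- Power = Φ(2.316 − critical value).

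| | alpha 0.05 (1.960) | alpha 0.05/6 (2.638) |
|---|---|---|
| All 900 | 64% | 37% |
| 25% attrition (168.75 per arm per half; SE 0.0748, z = 2.006) | 52% | 26% |

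**6. Sensitivity to the control rate.** The same formula with all 900 and alpha 0.05/6:

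| Control rate | SE | Power |
|---|---|---|
| 10% | 0.0492 | 66% |
| 20% | 0.0583 | 48% |
| 30% | 0.0634 | 39% |
| 50% | 0.0648 | 37% |
| 60% | 0.0612 | 43% |

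So a large interaction would more often than not be left undisplayed at control rates from 20% to 60%, but not at 10%.

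**The case against.** **The error rate is addressed.** The subgroup section sits under Statistical analysis, which sets 5% for primary-outcome hypotheses and commits to family-wise control. A reader might infer that the interactions are tested with no error control; the text does not support that. The rule may well cover them, and the exact family and method can be left to the full protocol or the statistical analysis plan. This stands. What remains is that the article does not say whether the rule applies and that an open list leaves the number of tests undefined.

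**A false moderator is not likely.** A reader might infer that one will probably be presented as real. The figures are about 5% with adjustment and 18% to 26% without, well short of an even chance. Nothing in the article says that a significant interaction will be treated as confirmed. Its models are described as exploring relations, and probing an interaction only after it passes a test is ordinary practice. This stands.

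**The 90% is not a claim about moderators.** A reader might take it as a false power claim for race/ethnicity or gender. The same paragraph ties its term to the individual tests, and the figure is right for them. This stands; the label is merely loose, because Aims and objectives and Secondary outcomes call the same analyses secondary.

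**Non-significant results are not expressly suppressed.** All interactions will be modelled, outcomes by race/ethnicity and gender are promised unconditionally, and the open list could admit gender. This is fair, but only in part. The one display rule given for the moderators is conditional on significance, and the unconditional promise covers only race/ethnicity and gender.

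**Low interaction power is normal** in a trial sized for a main effect. That is true, and it is a reason not to let significance decide what is shown.

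**Conclusion.** The point holds as a weakness in a stated analysis rule, not as an absence of error control. Display is triggered by significance and the list is open. Gender is missing from the section where it belongs.

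The two readings of the family-wise rule have different costs. If it covers the interactions, false moderators are held near 5%, but a large real interaction would be shown in about 37% of trials (26% with a quarter lost and excluded). If it does not, about 18% to 26% of trials would show at least one false moderator on a single outcome, and even at 5% the same real interaction would be missed in about 36%.

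The power figures rest on an assumed 35% control rate, an even split, effects of 7.5 and 22.5 points, and a normal approximation. The false-positive range rests on five or six tests, one outcome, and correlation from none to 0.5. The case for unconditional display does not depend on any one of these values. The primary comparison and the stated power figures are unaffected.

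**What to change.** 1. In Subgroup analyses, close the list at six moderators: site, ethnicity, education, insurance status, acculturation and gender.
2. Replace the significance-triggered rule. For every level of each moderator, report the arm effect as a risk difference with 95% CI, together with the interaction estimate and its p-value, whether or not significant. Acculturation, if kept continuous, needs prespecified levels or values at which the effect is shown.
3. State that these results are read as exploratory.
4. Minor wording: in Sample size calculation, call the 1.25% analysis the secondary analysis of each individual test, to match Aims and objectives and Secondary outcomes. Its 90% power figure can stay.

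The cost is some wording and one extra table or forest plot. Gender and the other moderators are already part of the planned analyses, so no added participants are needed. The downside is that a significant interaction is reported as hypothesis-generating rather than as a finding.

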#### Data monitoring

A Data Safety and Monitoring Board (DSMB) is required for all clinical trials at the University of Miami’s Sylvester Comprehensive Cancer Center (SCCC). These reviews are conducted by a standing committee (DSMC). The DSMC functions as an independent body, providing analysis of efficacy data and interim reviews of safety monitoring. DSMC membership consists of experienced investigators representing multiple specialties/disciplines. Sixty percent of current DSMC faculty members hold the rank of associate or full professor level and provide DSMC mentorship to assistant-level faculty members. The DSMC has full authority to require amendments to a study, suspend any study falling below DSMC standards, and/or provide recommendations to the Institutional Review Board (IRB) that the study be closed for lack of data integrity and/or patient safety reasons. Monitoring is conducted via monthly reports. Meetings are held on a monthly basis and trials with DSMC oversight are assessed based on the frequency associated with the assigned risk level. The DSMC report form provides an institutional mechanism for a protocol summary review and is the basis for reviewer evaluation of subject safety and trial conduct.

#### Adverse events

The study team will collect information and monitor any adverse events, including any injury incurred as a result of self-testing. If an adverse event occurs, participants will be immediately referred to appropriate medical care, and the study team will report the event to the principal investigators (PIs) and the IRB. Information regarding adverse events will be recorded in REDCap.

#### Protocol approvals and amendments

The current study was approved by the University of Miami IRB. There have been 13 minor amendments to update study documents, such as adding staff to the protocol (version date: October 15, 2019). Since the study began, there have been no changes in primary or secondary outcomes.

#### Informed consent

CHEs obtain informed consent in the participant’s preferred language (the informed consent document available in English, Spanish, and Haitian Creole, and CHEs are bilingual), and will answer all participant questions and ensure participant comprehension prior to obtaining signatures. For participants with limited literacy, the CHEs will read the consent verbatim with a witness present to ensure no bias enters the consent process.

#### Confidentiality

To protect confidentiality, all participants are assigned a study ID number and only this number (no identifying information) is included on study assessments. Datasets will be de-identified prior to analysis, and all study data will be stored on secure servers. In addition, any paper files are stored in locked file cabinets in secure office spaces.

#### Access to data

Regarding access to data, only the data manager and study biostatistician will have access to raw data files. If necessary, the data manager may share cleaned and de-identified data with other study staff for ongoing data analysis and monitoring such as for the creation of tables and charts. Investigators outside the study may request access to de-identified datasets through the study PIs.

#### Post-trial care

As noted above, all participants who screen positive for any of the four conditions are navigated by the CHW to free or low-cost follow-up care, and CHWs follow-up with these participants to ensure appointments are made, and to address any barriers to obtaining follow-up care. Additionally, regardless of study allocation, any participants who have completed the study and remain unscreened at the 6-month follow-up assessment are offered either home-based screening or navigation to a provider for screening by the CHW, based on participant preference. However, to avoid any bias or interference with intervention completion, participants are not previously informed that the screenings will be offered at the conclusion of the study. This post-study testing will not be part of data analysis.

#### Dissemination

While we will share our findings through academic channels such as journals and conferences, as consistent with CBPR, we will also share our results with the study communities. To aid with this process, community partners will help disseminate our study findings through culturally appropriate communication channels, such as organizing a series of community forums.

## Discussion

Our project addresses the excess burden of HIV, HCV, CRC, and cervical cancer experienced by Little Haiti, Hialeah, and South Dade, three medically underserved communities within the Miami metropolitan area. Using a CBPR approach, we will determine the effectiveness of navigation to primary care for screening versus CHW-delivered, home-based, multimodality screening among 900 individuals from our target communities. Study findings will allow us to optimize this for disease screening in real-world settings.

There are several study limitations that should be considered. There is only one CHW per community, which impedes our ability to determine whether potential differences in intervention effectiveness by community are due to community or CHW-related factors. We apply regular monitoring and quality control to maximize fidelity among study CHWs. Moreover, the CHW encounter logs may be used to better understand the influence of CHW-related factors on study outcomes. Our results also may not be generalizable outside of our target communities, as the current intervention approaches are heavily tailored based on community partner input. While this approach is a valid method of addressing health disparity within these specific communities, the effectiveness of multi-modality home-based testing would likely need to be re-examined if implemented outside of our target communities. Lastly, our primary outcome is based on self-report. However, self-reported data may overestimate the proportion of persons who obtained the screenings. For participants in the HBT group who choose home testing, we will have objective lab data to validate their self-reported data. However, if participants in the PC group overestimate their screenings, it could bias our results towards the null hypothesis.

## Trial status

The first trial participant was enrolled on June 26, 2017. As of January 2020 we have enrolled 705 of our target 900 participants in the study. The trial is projected to end in December 31, 2020. The current protocol is version #5, November 19 2018.

## Data Availability

Not applicable.

## Abbreviations

CBPR: Community-based participatory research
CHE: Community health educator
CHW: Community health worker
CRC: Colorectal cancer
DSMB: Data Safety and Monitoring Board
FIT: Fecal immunochemical test
FQHC: Federally qualified health center
HBT: Home-based testing
HCV: Hepatitis C virus
HPV: Human papilloma virus
IRB: Institutional Review Board
PC: Primary care
PCP: Primary care provider
PI: Principal investigator
RA: Research assistant
UM: University of Miami
USPSTF: United States Preventive Services Task Force
